### Methods for additional analyses (e.g., subgroup analyses) {20b}

Use machine learning to identify subgroups or predictors of differential treatment effects:Use causal forests to estimate treatment effect heterogeneity [16].Outcomes:Identify groups for which the treatment effect is stronger or weaker.Generate hypotheses about interaction terms for inclusion in traditional models.

Given our study’s limited power, subgroup analyses will be exploratory, estimated via treatment and covariate interaction terms at the individual level. Subgroup analyses will use “honest” estimation approaches (e.g., sample splitting to separate model training from estimation) from the causal machine learning literature to avoid over-interpretation, and results will be interpreted cautiously using established frameworks such as the ICEMAN tool to assess credibility [17].

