## Introduction

### Background and rationale {6a}

Despite significant advances in global childhood vaccination, immunization rates in many parts of the world remain insufficient. Vaccine disparities are particularly evident in low- and middle-income countries (LMICs), where coverage against diphtheria, pertussis, and tetanus—a key indicator of access to routine vaccination services—falls below 50% in many regions [1]. Coverage gaps have been further widened by the COVID-19 pandemic [2]. Barriers to vaccine distribution and utilization in LMICs include inadequate health facilities and local public health infrastructure, unreliable vaccine supply, storage, and transport capabilities, and lack of health care provider and/or proxy availability and training [3]. Behavioral and social drivers of vaccination are similarly important and include perceived disease risk, vaccine confidence, and social norms [4].

Although public approval of childhood vaccines is generally high in LMICs, there may be regional variations in acceptance and uptake that reveal inequities in vaccine access and/or confidence. According to the SAGE (Strategic Advisory Group of Experts on Immunization) Working Group on Vaccine Hesitancy, this lack of confidence may be manifested as vaccine hesitancy, defined as delay in acceptance or refusal of vaccines despite the availability of vaccination services [5]. Vaccine hesitancy is complex and content-specific and may be attributable to low levels of trust in vaccines and/or delivery systems; low perceived risk of vaccine-preventable disease; or barriers to accessibility, affordability, and availability, among other issues [6]. While health workers remain trusted sources of vaccine information and key influencers in immunization decision-making, they may face significant time constraints and resource limitations that impair their ability to administer vaccines and/or provide needed counseling. A major challenge, therefore, is the shortage of individuals who are culturally competent and equipped to administer vaccines and provide counseling. Ensuring that these individuals are well-trained and closely connected to the local communities they serve is critical.

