### Sample size {14}

For this cluster randomized control trial, we specified a stepped wedge design with baseline measures and a cross-sectional sampling structure. The primary outcome is the net difference between arms in repeated cross-sectional samples. We used the following parameters for sample size calculation: (a) type I error rate: 0.05; (b) power: 0.80; (c) expected vaccination proportion in controls: 49.5% (based on the 2022 survey); and (d) intraclass correlation coefficient (ICC): 0.0816 (based on the 2022 survey).

To detect a 13 percentage point increase in vaccination coverage (62.5% in the intervention arm vs. 49.5% in the control arm), we determined that 100 individuals per cluster are required. With a stepped wedge design involving three clusters in the first year and three in the second year, this sample size provides adequate power to detect the specified effect size. The sample size calculation assumed an exchangeable (time-invariant) intracluster correlation; no temporal decay was assumed.

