### Primary outcome analysis: mixed-effects logistic regression

To evaluate the primary outcome, we will use a generalized linear mixed model (GLMM) model with a logit link, including period-fixed effects and a cluster-level random intercept to account for intracluster correlation. The outcome of full vaccination will be specified as the dependent variable, with experimental condition as a dummy variable to estimate the treatment effect.

We will include data from all years and all clusters, adjusting for time and covariates

$$\begin{aligned} logit(P({Y}_{ijk}=1))={\beta}_{0} &\,+{\beta}_{1}\cdot Treatment_{jk}+\gamma_{1}1\{k=1\}\\ &\,+\gamma_{2}1\{k=2\} + X_{ijk}^T\beta_2+{u}_{j} \end{aligned}$$

$${\beta }_{1}$$: treatment effect (log-odds)

$${\gamma }_{k}$$: time trends independent of the treatment, where $$\textrm{k} \in \{1,2\}$$

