### Secondary analysis: time-by-treatment interaction

To test whether the intervention effect varies over time, we will include interaction terms between treatment and period. As no clusters are treated in Year 0 (baseline) and all are treated in Year 2, we parametrize the model with interaction terms and period fixed effects.

$$\begin{aligned}&logit(P(Y_{ijk}=1))\\ \quad \quad \quad \quad \quad & =\beta_0+\gamma_1 1\{k=1\}+\gamma_2 1\{k=2\} \\\quad \quad \quad \quad \quad &+ \beta_{11}(Treatment_{jk}\times 1\{k=1\}) \\\quad \quad \quad \quad \quad &+ \beta_{12}(Treatment_{jk}\times 1\{k=2\})\\\quad \quad \quad \quad \quad &+X_{ijk}^T\beta_2+u_j\end{aligned}$$

$$\beta_{11}$$ and $$\beta_{12}$$ are treatment effects (log-odds) in Year 1 and Year 2 respectively. We will conduct additional analyses for which we have no directional hypothesis or preliminary data to guide sample size considerations. Analyses of our secondary outcomes listed in Table 2 (e.g., specific vaccines, vaccination attitudes) will use analogous GLMMs appropriate to the outcome type. We will also conduct mediation analyses, to ascertain if the secondary outcomes are on the mediation pathway between the experimental conditions and the primary outcome. We will also do subgroup analysis based on individual-level characteristics (e.g., age, gender, baseline covariates). All data will be analyzed in R or SAS.

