### Adverse event reporting and harms {22}

This study is a cluster randomized control trial, with districts receiving different vaccine-related interventions, including a MVC and religious conference. While individuals within those districts may benefit from these interventions, the individual participants in the study may or may not experience direct benefits.

The primary risk associated with the study is the potential loss of confidentiality regarding participants’ children and their vaccination information. However, this risk is considered low, as the data collected during the study is not highly granular. Additionally, we have established a robust data protocol to minimize this risk. We will store all questionnaires in a password-protected folder on Dropbox, a HIPAA-compliant platform supported by the University of Michigan.

We have structures in place to manage and address potential negative reactions. Although we do not anticipate adverse reactions, as the interventions—MVCs and religious conferences—are extensions of well-established public health programs, the research team remains prepared to respond. As a team of researchers in the USA and Indonesia, we will regularly be in contact to discuss this project. Indonesian researchers have already engaged community members, including religious leaders and public health workers, to promote transparency and build trust. As part of a community-engaged approach, the Indonesian team will conduct quarterly follow-ups with stakeholders to assess the intervention’s effectiveness, identify any concerns, and address potential negative reactions. If we observe adverse trends, such as reduced vaccination uptake or increased vaccine hesitancy linked to the interventions, we will pause the implementation to investigate further. We will identify specific subpopulations showing negative reactions and organize focus groups to explore the underlying causes and inform modifications to the interventions.

These strategies will ensure that risks are actively mitigated, and any harms are promptly addressed to safeguard the well-being of participants and the broader community.

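### Subgroup models that add only treatment-by-covariate terms to shared period effects pass two-thirds of any differential 2023–2025 trend into the interaction

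*Protocol article*

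**What the plan says.** The primary model is a logistic mixed model "including period-fixed effects and a cluster-level random intercept". Its printed equation has one treatment term, two year indicators (gamma1 and gamma2) shared by all children, covariate main effects and a district intercept. The equation for the time-by-treatment analysis keeps the same shared year indicators. That section also plans subgroup analyses on individual characteristics, with age and gender named first.

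Section {20b} describes how subgroup effects are obtained: "subgroup analyses will be exploratory, estimated via treatment and covariate interaction terms at the individual level". It adds causal forests, whose output may suggest interaction terms for the conventional models, honest sample splitting, and a credibility tool for cautious reading. No printed model contains a period-by-covariate term.

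The article states the design feature that matters here: "As no clusters are treated in Year 0 (baseline) and all are treated in Year 2". Table 1 shows three of six districts treated in 2024 in each of the two trials.

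**The concern.** Treatment and calendar year are strongly linked in this design. The primary model deals with this through its period effects, which absorb any change common to all children. They cannot absorb a change that differs between subgroups. If the only subgroup-specific term is treatment-by-covariate, it picks up that change.

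Age shows how this could arise. Children aged 1–2 in September 2023 were born between October 2020 and September 2022, and they are the children aged 3–4 in September 2025. If coverage in that birth cohort differs from its neighbours, the age groups move apart between surveys with no intervention effect. The Background says "Coverage gaps have been further widened by the COVID-19 pandemic", but it speaks of low- and middle-income countries generally and gives no figure by birth cohort or for Aceh.

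At stake is an apparent finding that the intervention works better in one subgroup, when only the calendar trends differ. Honest splitting guards against overfitting. It does not help here, because the link between treatment and year is the same in both halves of a split.

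**Working it through.** **Inputs from the article.** Each trial has 6 districts and 3 surveys, three districts following the pattern 0,1,1 and three 0,0,1 (Table 1). From Sample size {14}: 100 individuals per cluster, read as per district per survey; exchangeable ICC 0.0816; "62.5% in the intervention arm vs. 49.5% in the control arm"; "type I error rate: 0.05", taken as two-sided.

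**Assumptions.** Two equal subgroups (50 children per district-survey cell), no true effect, total variance 0.56 × 0.44 = 0.2464 (0.56 is the midpoint of 0.495 and 0.625), and a differential trend D, which the article does not give.

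**1. The plan's own power.** The Hussey–Hughes variance is Iσ²(σ² + Tτ²) / [(IU − W)σ² + (U² + ITU − TW − IV)τ²], with I = 6, T = 3, U = 9, W = 45, V = 15.
- τ² = 0.0816 × 0.2464 = 0.0201 and σ² = 0.9184 × 0.2464 / 100 = 0.00226.
- The bracketed coefficients are 54 − 45 = 9 and 81 + 162 − 135 − 90 = 18.
- Variance = 0.00222, SE = 4.7 points, and 13 / 4.71 = 2.76, so power is about 0.79.

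Other choices of the proportion give 0.782 to 0.794. The stated 0.80 is reproduced within 2 points, so these inputs describe the planned design.

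**2. How much trend passes through.** Let the coverage difference between subgroups, relative to 2023, be 0, m and D in the three surveys.
- Nine untreated district-years (six in 2023, three in 2024) average 3m/9 = m/3.
- Nine treated district-years (three in 2024, six in 2025) average (3m + 6D)/9 = (m + 2D)/3.
- The treatment-by-subgroup coefficient is the difference, **2D/3**, whatever m is.

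Closed-form weighted least squares gave 0.667 for subgroup shares of 20%, 50% and 80%. Logistic fits to expected proportions, at shares of 20% and 50%, gave 0.63 to 0.68 of D.

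**3. What each subgroup shows.** The shared period effects keep the average treatment effect at its true value of zero. With share p in the changing subgroup, the apparent effects are therefore +(2/3)(1 − p)D there and −(2/3)pD in the other. At p = 0.5 and D = 10 points these are +3.3 and −3.3 points.

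**4. Precision and false positives.** Subtracting the two subgroup means within a district-survey removes the district intercept. The variance is v = 2 × 0.2464 × 0.9184 / 50 = 0.00905. The SE of the interaction is √(v/S), where S is the treatment variation left after the other subgroup terms.
- As described: S = 18 × 0.25 = 4.5, so SE = 4.5 points.
- With period-by-subgroup terms: only 2024 contributes, S = 6 × 0.25 = 1.5, so SE = 7.8 points (ratio √3 = 1.73).
- With district-by-subgroup terms as well: S = 6 × (1/36 + 4/36 + 1/36) = 1, so SE = 9.5 points.

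| Assumed D | False interaction | Nominal p<0.05 |
|---|---|---|
| 5 points | 3.3 points | 10–12% |
| 10 points | 6.7 points | about 30% |
| 15 points | 10 points | 56–61% |

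For 10 points, 6.67 / 4.48 = 1.49 gives 32% by normal approximation. Two separate logistic simulations gave 28% (3,000 trials) and 33% (250 trials). With period-by-subgroup terms the bias is zero, and rejection was 4.5–5.8% and 4.4–6.8% in those simulations.

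**5. If the planned effect is real.** On the logit scale, 49.5% to 62.5% is 0.531 and a 10-point trend (49.5% to 59.5%) is 0.405. The other subgroup then shows about 0.40 instead of 0.531. At equal shares its sign reverses only if D exceeds about 3 × 0.531 = 1.59.

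**The case against.** The strongest reply is that the fault is read from silence. Section {20b} prints no subgroup equation and does not say that treatment-by-covariate terms are the only ones added. The full protocol or the code could contain more. That stands as a limit: a reader might infer that the article rules out period-by-covariate terms, and it does not. But the article does say how subgroup effects are estimated, and adding the named terms to the printed models gives the biased result. This is more than an omitted detail.

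The calculation covers the regression models only. The article does not say how survey year enters the causal forests, so nothing is claimed about them.

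There is also a fair point about accuracy. With a 5-point trend, the root mean square error is √(3.3² + 4.5²) = 5.6 points as described, against 7.8 with the added terms. The two are equal near D = 9.5 points. For small trends the added terms therefore lose accuracy. What they restore is a valid test and an interval that reflects what the design can support.

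A reader might connect this to the harms section, which says "We will identify specific subpopulations showing negative reactions and organize focus groups". The documents do not support that link. The section relies on stakeholder follow-up and observed adverse trends and does not mention the {20b} models. The two-thirds figure also needs the September 2025 survey, which follows the last planned outreach round in May–June.

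**Conclusion.** The concern holds conditionally. If the subgroup regressions are built from the terms the article names, effect modification is confounded with calendar year, and the share passed through is two-thirds: exact on the linear scale and close to it on the logit scale.

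The practical size depends on D, for which the documents give no value. A trend common to all subgroups does no damage. Lower coverage in the 2020–2022 birth cohort is a possibility, not something the article reports.

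A reader might infer that the plan will generally show false harm in one subgroup. The calculation does not support that. Under no true effect and a 10-point trend, significant harm appeared in 10% of simulated trials, and under the planned 13-point effect that subgroup's benefit is only understated.

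The analyses are labelled exploratory, so this is a matter of correct specification for secondary results. The exploratory label and the credibility tool encourage caution, but they do not remove the bias.

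**What to change.** State in {20a} and {20b} that every regression subgroup model includes subgroup × 1{k=1} and subgroup × 1{k=2} alongside treatment × subgroup. Beside each result, show subgroup coverage by survey year and start sequence, so that a reader can see whether trends differ.

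This takes a sentence or two and no new data. The cost is the wider interval shown above, which the report should acknowledge. A district-by-subgroup intercept is not needed to remove the time bias. It can be an optional sensitivity analysis, with an SE of up to about 9.5 points.

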### Methods in analysis to handle protocol non-adherence and any statistical methods to handle missing data {20c}

Our main analysis will be based on participants who have provided all required information for the primary outcome.

### Plans to give access to the full protocol, participant-level data, and statistical code {31c}

The full protocol is publicly available: 10.6084/m9.figshare.25991875. Statistical code will be uploaded with each manuscript. The de-identified participant-level dataset will also be made publicly available.

## Oversight and monitoring

### Composition of the coordinating center and trial steering committee {5d}

The research teams in Indonesia (led by [name]) and the USA (led by [name]) provide day to day support for the trial. The team in Indonesia meets weekly, and the two sides meet every 2 weeks during intensive data collection and trial implementation periods, otherwise monthly.

### Composition of the data monitoring committee, its role and reporting structure {21a}

Because we are examining a group-level outcome, a data monitoring committee is not applicable.

### Adverse event reporting and harms {22}

This study is a cluster randomized control trial, with districts receiving different vaccine-related interventions, including a MVC and religious conference. While individuals within those districts may benefit from these interventions, the individual participants in the study may or may not experience direct benefits.

The primary risk associated with the study is the potential loss of confidentiality regarding participants’ children and their vaccination information. However, this risk is considered low, as the data collected during the study is not highly granular. Additionally, we have established a robust data protocol to minimize this risk. We will store all questionnaires in a password-protected folder on Dropbox, a HIPAA-compliant platform supported by the University of Michigan.

We have structures in place to manage and address potential negative reactions. Although we do not anticipate adverse reactions, as the interventions—MVCs and religious conferences—are extensions of well-established public health programs, the research team remains prepared to respond. As a team of researchers in the USA and Indonesia, we will regularly be in contact to discuss this project. Indonesian researchers have already engaged community members, including religious leaders and public health workers, to promote transparency and build trust. As part of a community-engaged approach, the Indonesian team will conduct quarterly follow-ups with stakeholders to assess the intervention’s effectiveness, identify any concerns, and address potential negative reactions. If we observe adverse trends, such as reduced vaccination uptake or increased vaccine hesitancy linked to the interventions, we will pause the implementation to investigate further. We will identify specific subpopulations showing negative reactions and organize focus groups to explore the underlying causes and inform modifications to the interventions.

These strategies will ensure that risks are actively mitigated, and any harms are promptly addressed to safeguard the well-being of participants and the broader community.

### Frequency and plans for auditing trial conduct {23}

We do not currently have plans to audit the trial.

### Plans for communicating important protocol amendments to relevant parties (e.g., trial participants, ethical committees) {25}

Not applicable (the study is repeated cross-sectional in design).

### Dissemination plans {31a}

We note no publication restrictions. Findings from the study will be publicized on the funder (Center for Global Health Equity) website, in peer-reviewed manuscripts, and in technical reports tailored to an Indonesian audience.

## Discussion

The TABRIE trial seeks to address persistent challenges in improving pediatric vaccination rates by targeting both logistical barriers and societal factors. By combining mobile vaccine delivery with tailored engagement through religious leaders, the trial offers an innovative approach to integrating vaccination services into community settings. The stepped wedge cluster randomized design is particularly suited to this context, allowing for the equitable and phased rollout of interventions while providing robust internal validity for assessing their effects on vaccination rates and parental attitudes.

The trial builds on global evidence demonstrating the importance of integrating vaccination into familiar social spaces, such as religious institutions, schools, and community centers, to counteract barriers like vaccine hesitancy and access limitations. Past successes of MVCs and culturally tailored counseling—seen in Pakistan, Boston, and elsewhere—support the potential of this model. TABRIE extends these approaches by engaging religious leaders and community health workers in Aceh, Indonesia, to provide culturally sensitive counseling and increase trust in vaccination services. This dual strategy addresses the intertwined barriers of logistical inaccessibility and misinformation that disproportionately affect underserved populations.

Operational challenges emerged during year 2, particularly in the Jaya Baru district of Banda Aceh, where some healthcare workers refused to cooperate with the study team. While other villages within Jaya Baru permitted the intervention, the district could not be replaced due to its prior exposure to treatment and the structure of the trial design. To account for this, we will conduct sensitivity analyses using a “leave-one-out” approach to evaluate the robustness of our findings with and without data from Jaya Baru. Although these analyses may have limited power, they will provide valuable insight into the potential impact of this issue.

This trial contributes to a growing body of work emphasizing the importance of tailoring vaccination delivery strategies to local contexts. By combining evidence-based logistical interventions with culturally appropriate outreach, TABRIE aims to provide practical and scalable solutions for increasing vaccine uptake. Its findings will offer actionable insights for policymakers and practitioners seeking to address vaccine hesitancy and improve immunization coverage in similar low-resource settings.

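### The Jaya Baru check removes all three surveys for a Year 2 problem; removing only its Year 2 sample isolates that problem at about a fifth of the variance cost

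*Protocol article*

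**What the plan says.** The Discussion reports: "Operational challenges emerged during year 2, particularly in the Jaya Baru district of Banda Aceh". It adds that the intervention went ahead in other villages of the district and that the district could not be swapped out because it had already been exposed. The remedy is a leave-one-out sensitivity analysis to "evaluate the robustness of our findings with and without data from Jaya Baru", which the authors expect to have limited power. The text does not confine the exclusion to Year 2.

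Table 1 (Trial design {8}) lists Jaya Baru as an MVC district treated in years 1 and 2, so it is one of three early-start districts out of six. The two interventions are analysed as separate trials.

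The primary model uses all years and clusters, period fixed effects, a district random intercept and one constant effect, "with experimental condition as a dummy variable to estimate the treatment effect". The time-by-treatment section confirms that every district is treated in Year 2. No section states which way the Jaya Baru problem would move the estimate.

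**The concern.** The reported problem touches one of the 18 MVC district-surveys (6 districts × 3 surveys). The planned check removes three, including Jaya Baru's Year 1 sample. Year 1 is the only survey in which treated and untreated districts coexist, so it carries the largest weight in the effect estimate.

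Two things are at stake. The first is precision, in a trial with six districts. The second is interpretation. If the estimate moves when the district is removed, the analysis cannot tell whether the Year 2 refusals caused the move or whether it came from losing one of only three early-start baseline-to-Year 1 contrasts. The check is meant to show the impact of the Year 2 problem, and it does not isolate it.

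A related matter is how the primary result will be read. Incomplete delivery is usually taken to dilute an effect. In this design that intuition should not be applied to an early-start district in Year 2.

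**Working it through.** **Inputs, all from Sample size {14} unless noted**
- "a) type I error rate: 0.05"; sidedness is not stated, two-sided used.
- "62.5% in the intervention arm vs. 49.5% in the control arm": a difference of 13 points, mean proportion 0.56.
- "intraclass correlation coefficient (ICC): 0.0816 (based on the 2022 survey"
- Correlation: "assumed an exchangeable (time-invariant) intracluster correlation; no temporal decay was assumed".
- "we determined that 100 individuals per cluster are required", read as 100 per district per survey.
- Six districts and three surveys; three districts follow the sequence 0,1,1 and three follow 0,0,1 (Trial design {8}, Participant timeline {13}).

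**Variance components on the risk-difference scale**
- Total: 0.56 × 0.44 = 0.2464.
- Between districts: τ² = 0.0816 × 0.2464 = 0.020106.
- Sampling variance of a district-survey mean: s² = 0.9184 × 0.2464 / 100 = 0.002263.

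**Reproducing the plan's power.** Let D₀, D₁, D₂ be the early-start minus late-start mean differences at the three surveys. Under the constant-effect model their expectations are 0, β₁ and 0. The generalised least squares (GLS) estimate is D₁ − b(D₀ + D₂), where

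b = τ² / (s² + 2τ²) = 0.020106 / 0.042475 = 0.473.

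Its variance is (1/3 + 1/3) × [τ² + s² − 2τ²b] = (2/3) × 0.003334 = 0.002223, so SE = 0.0471. Power is Φ(0.13/0.0471 − 1.96) ≈ 0.787, close to the stated 0.80. If 100 were the total over three surveys, power would be about 0.37, so that reading does not reproduce the plan.

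**Weight of each sample.** Dividing by three districts:

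| | Baseline | Year 1 | Year 2 |
|---|---|---|---|
| Early-start district | −0.158 | +0.333 | −0.158 |
| Late-start district | +0.158 | −0.333 | +0.158 |

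**Cost of each exclusion** (the single-sample row is the same GLS on the 17 remaining district-surveys):

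| Data used | Records | SE | Variance ratio | Power |
|---|---|---|---|---|
| All | 1,800 | 0.0471 | 1.00 | 0.787 |
| Without Jaya Baru Year 2 | 1,700 | 0.0482 | 1.05 | 0.769 |
| Without Jaya Baru | 1,500 | 0.0527 | 1.25 | 0.694 |

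The 1.25 follows from district counts alone, (1/2 + 1/3) / (1/3 + 1/3), so it does not depend on the ICC. The single-sample ratio is 1.02 at ICC 0.01 and 1.05 at ICC 0.20. With cluster autocorrelation of 0.9 to 0.5 it is 1.04 to 1.02, while the district ratio stays at 1.25.

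**Direction, conditional on a shortfall.** If measured Year 2 coverage in Jaya Baru is s points lower than it would otherwise have been, the estimate moves by −0.158 × (−s) = +0.158s:
- s = 3 (an assumption for illustration): +0.5 points.
- s = 13 (the whole design effect lost): +2.1 points, against an SE of 4.7 points.

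The Year 2 weight stays negative across the settings tried: −0.111 at ICC 0.01, −0.163 at ICC 0.20, and −0.139 and −0.103 at autocorrelation 0.8 and 0.5. On the logit scale, random-intercept models fitted to expected proportions (true log-odds ratio 0.531) gave estimates 0.075 to 0.087 higher when all of Jaya Baru's Year 2 effect was removed.

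**The case against.** Deleting a whole cluster is a standard influence check when there are only six. It asks whether the result hinges on this district, which is a fair question. It is supplementary to a primary analysis that keeps all the data, and the authors already concede its limited power. This stands: leave-one-out is valid and worth keeping. It is inefficient and poorly aimed at the stated problem, not wrong.

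The wording comes from the Discussion of a condensed article and does not list which surveys are dropped. That is true, but the article itself names leave-one-out of the district as its answer to a Year 2 problem, so the comment is on a stated choice.

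The interim model (baseline and Year 1 only) is untouched by Year 2. However, it is not planned as a Jaya Baru check, and discarding Year 2 in every district gives SE 0.0535, slightly worse than leave-one-out.

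A reader might go further and infer that the primary MVC estimate is biased upward, or anti-conservative, because of Jaya Baru. The document does not support that:
- It reports refusals and partial delivery, not a coverage shortfall.
- The outcome is cumulative in children aged 1–5, so children vaccinated in Year 1 and still in the age range remain vaccinated, and any shortfall may be small.
- The net direction depends on a constant effect across exposure years, which the protocol itself plans to test. If a second year of exposure adds d points, the constant-effect estimate falls below the first-year effect by 3 × 0.158d. A Jaya Baru shortfall s outweighs that only if s exceeds 3d. With d = 2 and s = 3, a first-year effect of 13 is estimated at about 12.5.
- The protocol nowhere claims that the analysis is conservative with respect to Jaya Baru.

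**Conclusion.** The point holds as one of targeting and efficiency. For a problem reported only in Year 2, the stated check costs 25% in variance and about 9 points of power, against 5% and about 2 points if only the affected sample is removed. It also cannot separate the Year 2 refusals from the loss of an early-start contrast. The absolute power figures rest on 100 per district per survey, the exchangeable ICC, a two-sided 5% test and a normal approximation. The variance ratios hardly depend on the ICC or on correlation decay.

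The statement about direction is conditional and modest: relative to no shortfall, lower measured Year 2 coverage in Jaya Baru would move the constant-effect estimate up by about 0.16 of the shortfall, at most about 2 points. That is enough to say dilution should not be assumed, and not enough to say the primary result is inflated. The Discussion says the problems arose particularly in Jaya Baru, which leaves open whether other districts were affected.

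**What to change.** - Pre-specify, as the main Jaya Baru sensitivity analysis, the primary MVC model with only that district's Year 2 sample excluded and its baseline and Year 1 samples kept.
- Keep full leave-one-out of the district as a second influence check, labelled as such.
- Leave the primary analysis as planned, with all data and the randomised treatment coding.
- Add one conditional sentence: in the constant-effect model an early-start district's Year 2 value has negative weight, so if non-cooperation lowered measured coverage there, the MVC estimate would move up rather than be diluted.
- State whether any other district-year had a comparable delivery problem and, if so, handle it the same way.

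The cost is a few sentences and one extra model run. The new check is slightly less precise than the full-data analysis (SE 0.048 against 0.047) and more precise than the one now planned.
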